## Abstract

**Background:**

Chemoradiation therapy (CRT) followed by surgery is currently the standard of care to treat patients with locally advanced rectal cancer (LARC). CRT reduces local recurrences, but is associated with significant damage to the surrounding healthy tissue that can severely impact patients quality of life. Additionally, a proportion of patients (hardly) benefit from CRT. We aim to develop a diagnostic innovation, using DNA-methylation, which can enable a more selective and thereby more effective use of the available therapies for rectal cancer patients.

**Methods:**

MeD-Seq Rectal is a prospective single centre, observational study. 75 patients diagnosed with rectal cancer and will receive CRT as neoadjuvant treatment are will be included. DNA-methylation profiling will be performed on liquid biopsies to predict pathological response to CRT.

**Discussion:**

To data no clinical or image-based features were found that predict response to CRT. we hypothesize that DNA methylation patterns in liquid biopsies may provide a promising and patient-friendly strategy to predict CRT resistance upfront.

**Trial registration:**

This trial is registered at ClinicalTrials.gov (NCT06035471).

## Background

Current guidelines in the Netherlands recommend to treat patients with locally advanced rectal cancer (LARC) with pre-operative radiotherapy combined with radio-sensitizing low-dose chemotherapy (CRT), followed by surgery. CRT clearly reduces the local recurrence rate in patients with LARC also when combined with newer surgical techniques such as the total mesorectal excision (TME) [1, 2]. However, with these newer surgical techniques the local recurrence rate is already below 10% and CRT only results in an absolute reduction of about ~ 5%. Effects of CRT on the development of distant metastases and overall survival appear to be limited at best. On the other hand, CRT can induce significant damage to the surrounding healthy tissue which may complicate subsequent surgeries and gives rise to late adverse effects severely impacting quality of life in patients treated for rectal cancer [3]. Although these late adverse effects are not reported systematically by all randomised controlled trials, irradiated patients significantly more frequently suffer from bowel - (up to ~ 60% of patients), and sexual dysfunction (~ 30% of patients) more than 6 months after surgery [3]. In addition, CRT was shown to almost double the risk for secondary malignancies after more than 5 years of follow up [2, 4]. Based on data from 4 randomized controlled trials Bakx et al. estimate that 5–13% of patients experience benefit from CRT without any harm, and 0–2% of patients have both benefit and harm. The majority of patients (74–87%) experiences neither benefit nor harm of CRT, whereas 6–11% of patients are only harmed by CRT without any benefit [5]. Notwithstanding the added value of CRT in a fraction of rectal cancer patients, tools that allow for careful patient selection are needed to reduce the number of patients that currently receive CRT without benefit but with potential serious long-term adverse effects. We hypothesize that detection of DNA methylation patterns in liquid biopsies may provide a promising and patient-friendly strategy to predict CRT resistance upfront.

## Methods

### Objectives

Primary Objective: To investigate whether we can predict pathological response to preoperative CRT by DNA methylation profiling in liquid biopsies. This study is still exploratory and will not have clinical consequences on the included patients of this study. The short term aim for this study is to find DNA methylation patterns in liquid biopsies to predict pathological response to CRT. If DNA methylation patterns can be found in this study to predict pathological response to CRT, in the future patients can be selected to receive CRT and patients can be saved from potential side effects when they are found to be non-responders to CRT.

Secondary Objective(s): To determine whether blood sampling after 1 week of CRT provides additional relevant information with respect to pathological response, and to investigate the associations between cell-free DNA (cfDNA) methylation and molecular characteristics of the tumour tissue. To investigate molecular characteristics of patients with a clinical complete response with a watch and wait approach after CRT.

### Study design

Observational, single centre, prospective study.

### Study population

#### Population

Locally advanced rectal cancer patients scheduled for preoperative CRT.

### Inclusion criteria

In order to be eligible to participate in this study, a subject must meet all of the following criteria:

Age ≥ 18 years.Histologically confirmed rectal adenocarcinoma.Scheduled for neoadjuvant chemoradiation.Written informed consent.

### Exclusion criteria

A potential subject who meets any of the following criteria will be excluded from participation in this study:

Scheduled to another neoadjuvant schedule that comprises systemic chemotherapy or short-course radiation.Not able to read or understand Dutch language or mentally not capable.

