For MeD-seq data, processing is carried out using specifically created scripts in Python, which include a trimming step to remove the Illumina adapters and a filtering step based on LpnPI restriction site occurrence between 13 and 17 bp from the 5’- or 3’ end of the read. Reads passing the filter are mapped to the genome using Bowtie 2. Using all unambiguously mapped reads count scores will be assigned to each individual LpnPI site in the genome. From genome-wide individual LpnPI site scores count scores are generated for 2 kilobase regions surrounding all known transcription start sites using a sliding window approach. To normalize potential differences in sequencing yields, regional read counts are divided by the total read count per sample. To generate a summary cfDNA methylation score, Z scores relative to healthy control samples (data already available from data of anonymous patients who donated blood at Sanquin and gave informed consent) will be calculated for every TSS region, which we will square and sum into a genome-wide Z score.

cfDNA methylation profiles and the summary score will be compared between patients with and without pathological response to CRT and, additionally, we will investigate associations between the cfDNA methylation profile/summary score, clinical, and molecular characteristics of the tumour.

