### Statistical analysis

All main analyses will be performed according to the intention to treat principle using appropriate statistical software, such as R Project for Statistical Computing version 4.0.4. (https://www.r-project.org/) and SPSS version 21.0 (SPSS inc., Chicago, IL). ctDNA methylation levels will be scored high/low relative to the median value in the cohort. Missing samples will not be replaced, because a dropout rate taken into account in the sample size calculation.

We will perform adaptive group-regularized logistic ridge regression followed by post hoc group-weighted elastic net feature selection as described before [10]. In this innovative method group-regularisation of all markers is based on auxiliary data that is provided separately to the model resulting in improved marker selection. In our case this auxiliary data will consist of tissue-based comparison measures like fold changes in DNA methylation and RNA expression between patients with and without a pathological response. When sufficiently promising a targeted assay can be developed for the most optimal marker panel to reduce costs and facilitate clinical implementation.

Obtained data from patients following a watch and wait approach due to a sustained clinical response will be analysed as a separate subgroup since in these patients no pathological response can be determined. These patients will also follow the regular follow-up and will be analysed conform the other patients, only as a subgroup.

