### Primary study parameter(s)

cfDNA methylation profiles and the summary score will be compared between patients with and without pathological response to CRT and, additionally, we will investigate associations between the cfDNA methylation profile/summary score, clinical, and molecular characteristics of the tumour. To obtain the most optimal panel of methylation markers predicting pathological response to CRT, we will perform adaptive group-regularized logistic ridge regression followed by post hoc group-weighted elastic net feature selection as described before [18]. In this innovative method group-regularisation of all markers is based on auxiliary data that is provided separately to the model resulting in improved marker selection. In our case this auxiliary data will consist of tissue-based comparison measures like fold changes in DNA methylation and RNA expression between patients with and without a pathological response. When sufficiently promising a targeted assay can be developed for the most optimal marker panel to reduce costs and facilitate future clinical implementation pending external validation of our findings. When available for the selected markers we will use publicly available data for this purpose and otherwise we will contact our network to find/collect a suitable sample cohort.

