## Discussion

To data no clinical or image-based features were found that predict response to CRT. Tissue-based analyses have been performed to find predictive molecular biomarkers for response to CRT, but to date none of the identified potential markers has been clinically implemented [11]. Gene expression panels were identified that allow for the discrimination between responders and non-responders [12, 13]. However, the need for fresh frozen pre-treatment tissue biopsies with sufficient tumour material hampers validation and subsequent clinical implementation of this type of predictive marker. Next to distinct gene expression profiles, high global DNA methylation levels in pre-treatment biopsies were associated with a poor response to CRT [14]. A biological rationale for this observation was provided by Thienpont et al., who showed that tumour-specific DNA methylation increases under hypoxia, which represents one of the major driving mechanisms behind radiotherapy resistance [8]. In contrast to RNA expression, DNA methylation provides a stable and robust biomarker, which facilitates subsequent validation and clinical implementation. Blood is known to contain circulating cfDNA from dying cells in the body, including ctDNA, rendering so-called liquid biopsies (i.e. blood sampling) a patient-friendly alternative to the traditional tissue biopsy. In addition, liquid biopsies are believed to more accurately reflect potential intra-tumour heterogeneity compared to a single tissue biopsy. The challenge is to distinguish ctDNA fragments from the total pool of cfDNA present in the blood. To date this is predominantly done using tumour-specific DNA mutations, limiting its application to patients carrying a known mutation in the tumour. Notwithstanding this limitation recent studies have shown that detection of ctDNA in the blood is predictive for disease recurrence [15], suggesting liquid biopsies could play a key role in the clinical management of rectal cancer patients. Data on the use of liquid biopsies to determine a tumour’s radio-sensitivity upfront is limited [16], but preliminary work suggests that high ctDNA levels before treatment start are associated with subsequent unresponsiveness of rectal cancer to chemo-radiation therapy. In addition, a spike in the ctDNA level directly after treatment start could reflect response to cytotoxic therapies such as radiotherapy [17]. Recent work by others and us demonstrates that tumour-derived DNA methylation profiles are also detectable in a patient’s blood [7], which is of particular interest for the current proposal considering the above mentioned link between increased DNA methylation levels and radiotherapy resistance. An additional advantage of DNA methylation over currently widely used mutations is the high prevalence of altered DNA methylation markers compared to mutations. Symonds et al. showed that ctDNA could be detected in 70% of pre-treatment blood samples from rectal cancer patients using only 2 methylation markers [18]. In conclusion, we hypothesize that DNA methylation patterns in liquid biopsies may provide a promising and patient-friendly strategy to predict CRT resistance upfront.

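### Patients with another active cancer are eligible, although the summary cfDNA score cannot separate that cancer's DNA from the rectal tumour's and may misplace such patients as methylation-high

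*Protocol article*

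**What the plan says.** All references are to the protocol article.

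- **Eligibility.** Inclusion criteria asks for adult age and "Histologically confirmed rectal adenocarcinoma.Scheduled for neoadjuvant chemoradiation.Written informed consent". Exclusion criteria has two entries: "Scheduled to another neoadjuvant schedule that comprises systemic chemotherapy or short-course radiation" and "Not able to read or understand Dutch language or mentally not capable". Neither list mentions a concurrent or recent other cancer.
- **Summary score.** Study procedures describes it as follows: "To generate a summary cfDNA methylation score, Z scores relative to healthy control samples" "will be calculated for every TSS region, which we will square and sum into a genome-wide Z score", with a bracketed note on the donors between these two parts.
- **High/low rule.** Statistical analysis states that "ctDNA methylation levels will be scored high/low relative to the median value in the cohort". I take the level to be the summary score, the only single-number measure defined.
- **Sizing.** Sample size calculation plans for a 2.5-fold difference in the chance of response between high and low patients, with at least 64 patients (75 with dropout).
- **Second predictor.** Primary study parameter(s) adds a marker panel: "To obtain the most optimal panel of methylation markers predicting pathological response to CRT, we will perform adaptive group-regularized logistic ridge regression". Rectal tissue comparisons guide the penalties.
- **Records.** Other malignancy is not among the patient characteristics in Other study parameters, nor among the risk factors in Secondary study parameter(s).

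**The concern.** The study wants a blood measure of the rectal tumour's sensitivity to CRT. The Discussion names the obstacle itself: "The challenge is to distinguish ctDNA fragments from the total pool of cfDNA present in the blood". The summary score does not address that obstacle for DNA shed by a second tumour. Squaring removes the sign of each deviation, so deviations cannot cancel. Summing over all TSS regions removes any tie to tissue of origin. The healthy-donor reference makes every cancer-related departure count.

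In a patient with two active cancers the score therefore reflects both and is biased upward. If that moves the patient over the cohort median, a label meant to describe the rectal tumour describes something else. Because the median split fixes the group sizes, a patient who is truly high is pushed into the low group in exchange. Both groups then move towards the average response rate.

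**Working it through.** **1. The plan's own figure.** Inputs from Sample size calculation: ratio 2.5, alpha 0.05, power 0.8 (the stated beta of 0.8 is read as power), chi-squared test with continuity correction, N = 64. Not given: the two response rates and the sidedness. I assume a two-sided test and solve for the rates. With p1 = 0.25 and p2 = 0.625 (difference d = 0.375, mean 0.4375):

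- uncorrected n per group = [1.960 × √(2 × 0.4375 × 0.5625) + 0.842 × √(0.1875 + 0.2344)]² / 0.375² = 26.26
- corrected n = (26.26 / 4) × [1 + √(1 + 4 / (26.26 × 0.375))]² = 31.4, so 32 per group and N = 64

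Rates from 24.3% v 60.8% to 25.6% v 64.0% come close to 64. Rates of 20% v 50% would need 90 patients and 30% v 75% would need 46. The dropout step, 64 / 0.85 = 75.3, agrees with the stated 75 to within one patient.

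**2. Worst case.** Let k of 64 patients have another active cancer, all scored high. Half of them would truly be low, so they respond at the average of 43.75%, and k/2 truly high patients spill into the low group:

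- high-group rate = [(32 − k) × 25% + k × 43.75%] / 32
- low-group rate = [(32 − k/2) × 62.5% + (k/2) × 25%] / 32

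For k = 3: (29 × 25 + 3 × 43.75) / 32 = 26.8% and (30.5 × 62.5 + 1.5 × 25) / 32 = 60.7%, a ratio of 2.27.

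Exact power sums the binomial probabilities over all tables that the corrected chi-squared test rejects. Formula power inverts the sample size formula. N needed restores 80% by that formula.

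| k (share of 64) | High | Low | Ratio | Exact power | Formula power | N needed | Exact power if the k are excluded |
|---|---|---|---|---|---|---|---|
| 0 | 25.0% | 62.5% | 2.50 | 83% | 81% | 64 | n/a |
| 1 (1.6%) | 25.6% | 61.9% | 2.42 | 80% | 78% | 68 | 79% |
| 2 (3.1%) | 26.2% | 61.3% | 2.34 | 77% | 75% | 72 | 81% |
| 3 (4.7%) | 26.8% | 60.7% | 2.27 | 74% | 71% | 76 | 78% |

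The result is the same if high methylation predicts better rather than worse response, because both groups shift by the same amount.

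**3. Milder case.** If the affected patients fall on either side of the median by chance, each group gains k/2 patients responding at 43.75%. For k = 2 the rates are (31 × 25 + 43.75) / 32 = 25.6% and (31 × 62.5 + 43.75) / 32 = 61.9%, with power of 80%. For k = 3 power is 79%. If the second tumour moves nobody across the median, nothing is lost.

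**4. Net value of excluding.** Worst case: 77% to 81% for two patients and 74% to 78% for three, roughly 4 points at most. For one patient there is no gain (80% kept, 79% excluded). With three placed by chance, keeping them (79%) is no worse than excluding them (78%).

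**The case against.** The strongest reply is that this is a design preference. The study is exploratory and observational, has no consequences for its participants, and broad eligibility for patients scheduled for CRT is defensible. The article contradicts nothing on this point, and handling of comorbid cancers may be left to the full protocol or SAP. That lowers the priority. It does not remove the point: the article presents its eligibility criteria as the conditions for entry, and the gap matters because of how this particular score is built.

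Four stronger readings are tempting, and the documents do not support them.

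- **Such patients always land in the high group.** The cut is the median of a cohort in which everyone has rectal cancer. A second tumour that sheds little DNA need not carry a patient over it. The score also still contains the rectal signal. The upward direction is supported, certainty is not.
- **The whole predictor is affected equally.** Regional profiles and the marker panel are also primary analyses, and the panel is steered by rectal tissue data. Its protection is only partial, because tissue guides the weighting while the inputs remain cfDNA values from the same patients.
- **An extreme score could dominate the sized analysis.** A median split ignores how extreme a score is. The article explicitly enters the summary score as continuous only in the exploratory Cox models, which also use the dichotomised version.
- **Deaths from the other cancer make OS wrong.** OS counts all deaths by definition, and its analysis here is exploratory.

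**Conclusion.** The point holds as a small, avoidable source of misclassification. The stated criteria admit patients with another active malignancy, the summary score cannot distinguish their second tumour from the rectal one, and no listed variable or analysis step would identify them. The bias in the score is upward, and its effect on the high/low contrast is dilution.

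With 1 to 3 affected patients among 64, the worst case is a ratio of 2.42 to 2.27 instead of 2.5, and power of 80% to 74% instead of about 83%. This rests on three assumptions that are not in the documents: the number affected, response rates of 25% v 62.5%, and placement of every affected patient in the high group. Chance placement gives a smaller loss. The case for acting is a cleaner label at little cost, since the recoverable power is small. I would treat it as optional but worthwhile.

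**What to change.** Add one line to Exclusion criteria: another active malignancy at baseline, apart from non-melanoma skin cancer and in-situ lesions.

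For patients already enrolled, record the same item as a flag. The electronic patient files and PALGA, both already named in Study procedures, can supply it. Report the summary-score comparison and the panel training with and without the flagged patients.

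The change needs no new sampling and does not touch treatment. Its cost is one criterion or one data item, plus a few fewer patients in the restricted analysis. With only one such patient the restricted analysis gains no power, which is a reason to show both results.

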### Sample size calculation

To detect a 2.5 fold difference in the chance of responding to CRT between circulating tumour DNA methylation high and - low patients with an alpha of 0.05 and a beta of 0.8, we need to include at least 64 patients according to the Chi-squared statistic with the continuity correction applied to compare proportions with a dichotomous outcome between two samples (http://www.sample-size.net/sample-size-proportions/). Based on previous and on-going studies we expect ~ 15% dropout due to either technical failure or loss to follow up. Therefore we will aim to include 75 patients in this project.

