### Main study parameter/endpoint

Pathological response rate (percentage necrosis in comparison to tumour cells in the resected specimen) after CRT, determined by an expert pathologist according to the Mandard Tumour Regression Grade (TRG).

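### The sample-size paragraph gives a beta of 0.8 where a power of 0.8 is almost certainly meant, and its 64 patients follow from a 2.5-fold ratio only once an unstated response rate is assumed

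*Protocol article*

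**What the plan says.** All the design figures stand in the protocol article under Sample size calculation.

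- Effect: "To detect a 2.5 fold difference in the chance of responding to CRT", comparing patients with high and low circulating tumour DNA methylation.
- Error rates and result: "with an alpha of 0.05 and a beta of 0.8, we need to include at least 64 patients". Sidedness is not given.
- Test: "Chi-squared statistic with the continuity correction applied to compare proportions with a dichotomous outcome between two samples".
- Target: with roughly 15% dropout expected, "Therefore we will aim to include 75 patients in this project".

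Under Statistical analysis, the two groups are formed by a median split: "ctDNA methylation levels will be scored high/low relative to the median value in the cohort". This makes them equal in size.

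The article gives no expected response rate, either overall or by methylation group. Main study parameter/endpoint names the Mandard grade but not the grade at which a patient counts as a responder, so no rate can be inferred from it. Power is not stated anywhere else.

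**The concern.** There are two faults in one sentence.

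First, beta is the probability of missing a true effect. A beta of 0.8 is a power of 20%, and nothing elsewhere in the article corrects it.

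Second, a test of two proportions needs two proportions. A 2.5-fold ratio could be 10% v 25%, 20% v 50% or 30% v 75%, and these need very different numbers of patients. As worded, the paragraph says that 64 patients suffice for a 2.5-fold difference whatever the response rate. A reader who accepts that could give a non-significant median-split comparison more weight than it can bear, if response turns out to be less common than the calculation assumed.

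**Working it through.** **Inputs.** From the article: alpha 0.05, ratio 2.5, continuity-corrected chi-squared test, 1:1 split, 64 in total (32 per group). Assumed here: two-sided alpha, power 0.8 in place of the printed beta, and the lower response rate p1, with p2 = 2.5 × p1.

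**Formula, per group.**

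n = [z(0.975) × √(2·p̄·(1 − p̄)) + z(power) × √(p1(1 − p1) + p2(1 − p2))]² / (p2 − p1)², where p̄ = (p1 + p2)/2

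With continuity correction: n_cc = (n/4) × [1 + √(1 + 4/(n(p2 − p1)))]²

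**Step 1: reproduce 64.** Take p1 = 0.25, p2 = 0.625 and power 0.8. Then p̄ = 0.4375 and the two square roots are 0.7016 and 0.6495.

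- n = (1.960 × 0.7016 + 0.8416 × 0.6495)² / 0.375² = 1.9217² / 0.1406 = 26.26
- n_cc = (26.26/4) × [1 + √(1 + 4/(26.26 × 0.375))]² = 6.565 × 2.1858² = 31.37, so 32 per group and 64 in total

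On this basis exactly 64 arises for p1 between 24.75% and 25.15%. At 25% v 62.5% the odds ratio is (0.625/0.375)/(0.25/0.75) = 5.0.

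**Step 2: take the printed beta literally.** With power 0.2, 25% v 62.5% gives n = 4.88 and n_cc = 9.46, so 10 per group and 20 in total. To reach 64 at 20% power the rates would have to be about 9% v 22.5% (n_cc = 31.78). A round 25% at 80% power is much the more plausible source of 64.

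**Step 3: other readings at 80% power.**

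- One-sided alpha with the correction: 64 arises at about 22% v 55%.
- Two-sided without the correction: at about 22.5% v 56%.
- An odds ratio of 2.5 in place of a ratio of proportions: 170 or more for lower rates of 10% to 55%, so never 64.

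**Step 4: how far the claim depends on the response rate.** In equal groups with ratio 2.5, p1 = 2 × overall rate / 3.5. Power below is exact, by enumerating both binomials with 32 per group and the two-sided continuity-corrected test. The last column is the total from the formula for 80% power.

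| Overall response | Low v high rate | Exact power, 64 patients | Total for 80% |
|---|---|---|---|
| 20% | 11.4% v 28.6% | 29% | 192 |
| 30% | 17.1% v 42.9% | 51% | 114 |
| 40% | 22.9% v 57.1% | 75% | 74 |
| 43.75% | 25% v 62.5% | 83% | 64 |
| 50% | 28.6% v 71.4% | 92% | 50 |

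The overall rates are illustrative. The formula's own approximate power at 25% v 62.5% is 81%; the exact figure is 83%.

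**Step 5: dropout.** 64/0.85 = 75.3 and 75 × 0.85 = 63.75. With 75 enrolled and 64 evaluable, 11 are lost, and 11/75 = 14.7%, which agrees with an approximate 15%.

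**The case against.** The strongest reply is that this is a one-word slip. Nobody plans a study for 20% power, and a round 25% reproduces 64 with the stated test, so the arithmetic is not shown to be wrong. A journal article may also leave the input rates to the full protocol. The study calls itself exploratory and without clinical consequences for its participants, and its marker panel comes from penalised regression, which does not rest on this calculation.

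Most of this stands, and it limits the weight of the point. It does not make the printed error rate correct. Nor does it support the claim as worded: the article itself says that 64 patients detect a 2.5-fold difference, without the condition that makes this true.

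A reader might infer more than the document supports:

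- *The study has 20% power.* That is the literal reading, but it needs rates of about 9% v 22.5%, which nothing in the article suggests.
- *64 patients are adequate at one response rate only.* Power rises above 80% at higher rates, and the back-solved pair itself moves with the unstated sidedness.
- *The study is underpowered.* The article gives no response rate, so nothing shows that the true rate lies below 44%. Watch-and-wait patients have no pathological response and would reduce the evaluable number, but no share is given from which to calculate the loss.
- *The target should be 76.* The difference from 75 is rounding within an approximate 15%.

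**Conclusion.** The point holds in a limited form. The stated beta is wrong as written and should read as a power of 0.8. The figure of 64 cannot be derived from the stated inputs. It is reproduced at about 25% v 62.5% (about 44% overall), given a two-sided alpha, the continuity correction and equal groups. That this pair was the authors' input is an inference.

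For the same ratio, the sensitivity of 64 patients depends strongly on how common response is, from 29% power at 20% overall to 92% at 50%. The unconditional claim therefore fails at lower response rates and is conservative at higher ones. Severity is minor to moderate: this is the only statement of the study's size and error rates, but correcting it changes neither the number of patients nor the conduct or analysis of an exploratory study.

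**What to change.** Reword the paragraph under Sample size calculation:

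1. Replace the beta of 0.8 with a power of 0.8 (beta 0.2).
2. State whether alpha is one-sided or two-sided.
3. State the response rate actually assumed in each methylation group, with its basis and the Mandard cut-off that defines response. If the input was 25% v 62.5%, say so, and give the overall rate of about 44%.
4. Limit the claim to a 2.5-fold difference at that response rate, and note that power is lower if response is less common.

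The target of 75 patients stays. The cost is one reworded paragraph, and a stated sensitivity that becomes conditional and less favourable than it now reads.
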